# Effects of small-dose S-ketamine on anesthesia-induced atelectasis in patients undergoing general anesthesia accessed by lung ultrasound: study protocol for a randomized, double-blinded controlled trial

**DOI:** 10.1186/s13063-023-07779-y

**Published:** 2024-01-18

**Keywords:** Atelectasis, S-ketamine, Ultrasound, Randomized controlled trial, Protocol

## Abstract

**Background:**

Atelectasis after anesthesia induction in most patients undergoing general anesthesia may lead to postoperative pulmonary complications (PPCs) and affect postoperative outcomes. However, there is still no existing effective method used for the prevention of perioperative atelectasis. S-ketamine may prevent atelectasis due to airway smooth muscle relaxation and anti-inflammatory effects. Lung ultrasound is a portable and reliable bedside imaging technology for diagnosing anesthesia-induced atelectasis. The primary objective of this study is to assess whether a small dose of S-ketamine can reduce the incidence of atelectasis after intubation, and further investigate the effects of preventing the early formation of perioperative atelectasis and PPCs.

**Methods:**

This is a single-institution, prospective, randomized controlled, parallel grouping, and double-blind study. From October 2020 to March 2022, 100 patients (18–60 years old) scheduled for elective surgery will be recruited from Beijing Tiantan Hospital, Capital Medical University, and randomly assigned to the S-ketamine group (group 1) and the normal saline group (group 2) at a ratio of 1:1. The label-masked agents will be administered 5 min before induction, and all patients will undergo a standardized general anesthesia protocol. Related data will be collected at three time points: after radial artery puncture (T1), 15 min after tracheal intubation (T2), and before extubation (T3). The primary outcome will be the total lung ultrasound scores (LUS) at T2. Secondary outcomes will include LUS in six chest regions at T2, total LUS at T3, arterial blood gas analysis results (PaCO_2_, PaO_2_) and PaO_2_/FiO_2_ at T2 and T3, and plateau pressure (P_plat_) and dynamic lung compliance (Cdyn) at T2 and T3. The incidence of postoperative complications associated with S-ketamine and PPCs at 2 h and 24 h after surgery will be recorded.

**Discussion:**

This trial aims to explore whether a simple and feasible application of S-ketamine before the induction of general anesthesia can prevent atelectasis. The results of this study may provide new ideas and direct clinical evidence for the prevention and treatment of perioperative pulmonary complications during anesthesia.

**Trial registration:**

ClinicalTrials.gov NCT04745286. Registered on February 9, 2021.

**Supplementary Information:**

The online version contains supplementary material available at 10.1186/s13063-023-07779-y.

## Background

Atelectasis refers to the complete or partial collapse of the entire lung or an area of the lung. Previous studies have reported that the incidence of pulmonary atelectasis during general anesthesia is as high as 85–90% [1]. It usually appears a few minutes after the application of 100% oxygen for pre-oxygenation and induction and continues until after surgery [1, 2]. Atelectasis plays an important role in the intrapulmonary shunt increase [3], gas exchange abnormalities, hypoxemia, and compliance decrease. These are associated with postoperative pulmonary complications (PPCs). It seriously affects the postoperative outcome in surgical patients [4–7].

The mechanism of perioperative atelectasis remains unclear. At present, the following three mechanisms have been mainly considered: compressive atelectasis, gas absorption, and alveolar surfactant destruction [2, 8–13]. The mechanism of atelectasis after anesthesia induction is mainly considered to be related to small airway closure and gas absorption in pre-oxygenated alveoli [14].

Ketamine and its S-isomer have been widely used in clinical anesthesia, especially in patients with sepsis or cardiovascular instability [15]. Ketamine and its S-isomer achieve anesthesia and analgesia primarily through non-competitive antagonism at N-methyl-d-aspartate receptors. For the different effects of other anesthetics, S-ketamine has effects on relaxing the bronchial smooth muscles and inhibiting inflammation, which may prevent atelectasis after anesthesia induction. Studies have shown that ketamine can relax bronchial smooth muscles in order to alleviate the closure of small airways, thereby significantly reducing ventilation resistance [16–18]. This effect is especially beneficial for patients with asthma and bronchospasm. Ketamine has a unique pleiotropic anti-inflammatory effect [19–22], which can prevent exacerbated pro-inflammatory reactions and extension of local inflammation mainly by inducing anti-inflammatory mediators such as adenosine [23]. These anti-inflammatory mediators inhibit the activation of nuclear factor NF-κB and repress the release of pro-inflammatory cytokines such as TNF-α, IL-6, and IL-8 [18, 23, 24]. In addition, it suppresses the activation and recruitment of leukocytes and precipitates the apoptosis of inflammatory cells in the lungs [25–27].

Among all the detection methods of pulmonary disease, lung ultrasound, as a bedside, non-invasive, diagnostic tool, has been increasingly used in the assessment of atelectasis during surgery. Furthermore, it has advantages such as convenience and rapidity and it is radiation-free [28–31]. It has a reliable sensitivity of 93% and specificity of 100% [32].

Previous studies on atelectasis during anesthesia mostly focused on the influence of respiratory parameters such as tidal volume, respiratory rate, inhaled oxygen concentration, positive end-expiratory pressure (PEEP), and the effects of manipulation or mechanical expansion on postoperative atelectasis [7, 33–35]. To date, there is only a little evidence available for pre-treatment with medicine for atelectasis during general anesthesia. The primary objective of this study is to assess whether a small dose of S-ketamine can reduce the incidence of atelectasis after intubation, and further investigate the effects of preventing the early formation of perioperative atelectasis and PPCs.

## Methods

### Trial design and study setting

This is a single-center, prospective, double-blind, parallel grouping, randomized controlled trial conducted at Beijing Tiantan Hospital, Capital Medical University, from October 2020 to December 2022. This study was approved by the Institutional Review Board of the Capital Medical University Hospital Institutional Review Board (IRB) and registered at ClinicalTrials.gov (trial registration number: NCT04745286). The patient flow diagram of the study is presented in Fig. 1, and the trial schedule is shown in Table 1.

**Fig. 1 Fig1:**
[figure not shown]
Flow diagram of the Consolidated Standards of Reporting Trials [36]. Group 1, S-ketamine group; group 2, normal saline group; T1, after radial artery puncture; T2, 15 min after tracheal intubation; T3, before extubation

**Table 1 Tab1:** The schedule of enrollment, interventions, and assessments

	**Study period**						
	Enrollment	Allocation	Postallocation				
Time point	Day − 1	Day 0	T1 (after radial artery puncture)	15 min after intubation (T2)	Before extubation (T3)	2 h after surgery	24 h after surgery
Enrollment							
Eligibility screen	X						
Informed consent	X						
Randomization		X					
Allocation		X					
Interventions							
[Group 1] S-ketamine group			X				
[Group 2] Normal saline group			X				
Outcome assessment							
Total LUS			X	※	X		
LUS of 12 chest regions				X			
PaCO_2_, PaO_2_, and PaO_2_/FiO_2_			X	X	X		
P_plat_ and Cdyn				X	X		
Incidence of postoperative complications associated S-ketamine						X	X
Incidence of PPCs						X	X

*LUS* lung ultrasound scores, *P*_*plat*_ plateau pressure, *Cdyn* dynamic lung compliance, *PPCs* postoperative pulmonary complications. ※ primary outcome

### Eligibility

The trial investigator will identify consecutive eligible patients according to the inclusion and exclusion criteria on the day before the operation. When the patients meet the eligibility criteria, the investigators will explain the study plan and relevant information to the participants.

#### Inclusion criteria

Age of 18–60 yearsAmerican Society of Anesthesiologists (ASA) physical status of I–IIPatients scheduled for urinary, obstetrics, and gynecology surgery in the supine or lithotomy position under general anesthesia with expected operation time of more than 1 hPatients and their authorized surrogates will sign an informed consent form

#### Exclusion criteria

Patients in whom the application of lung ultrasound is difficult, such as patients with chest fractures or a history of surgicalPatients with a history of upper respiratory tract infection 1 month before surgery or a history of smoking more than 6 packs/yearWhen the preoperative chest X-ray or CT results are abnormal, including atelectasis, pneumothorax, pleural effusion, or pneumoniaBMI > 30kg/m.^2^Expected difficulties in intubation or mask ventilationPatients with a significant increase in intraocular pressure and intracranial pressure before surgeryPatients who are allergic to S-ketamine, propofol, and opioidsPatients with a history of psychiatric disorders

#### Dropout criteria

Unexpected retention of the tracheal tube after operationReceiving a second operation during hospitalizationPerioperative complications such as pneumothorax and subcutaneous emphysema which make lung ultrasound assessment difficultWithdrawal during the trial

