### Criteria for discontinuing or modifying the allocated interventions

The assignment will not be modified; however, the study will be terminated in the following situations: (1) intraoperative serious adverse events, such as hemorrhage, shock, and malignant hyperthermia, and (2) without anticipated difficult airway or failure to extubation after surgery.

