### Interventions

Patients will be intravenously infused with the label-covered trial agent 5 min before induction, and all patients will undergo a standardized general anesthesia and analgesia protocol. Lung ultrasound scans will be performed at three points in each patient: immediately after radial artery puncture (T1), 15 min after tracheal intubation (T2), and before extubation (T3). Three arterial blood samples will be obtained through radial artery puncture at each time point (T1, T2, T3), and blood gas measurements will be performed immediately using a standard technique (ABL800).

Agent preparation method: S-ketamine group (group 1): S-ketamine (50 mg; 2 mL) will be diluted with normal saline to 5 mL in an opaque 5-mL syringe (10 mg mL^−1^). Normal saline group (group 2): 5 mL of normal saline. Both will be labeled as “study agents” and injected with a dose of 0.025 mL kg^−1^.

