#### Secondary outcomes

LUS in 12 chest regions (scans 1-6 in each hemihorax) at T2; total LUS at T3; arterial blood gas analysis results (PaCO_2_, PaO_2_) and PaO_2_/FiO_2_ at T2 and T3, P_plat_ and dynamic lung compliance (Cdyn) [Cdyn = tidal volume/(PIP-PEEP)] at T2 and T3; the incidence of postoperative complications associated with S-ketamine at 2 h and 24 h after surgery (visual impairment, dizziness, pathological irritability, nightmares, and hallucinations); the incidence of PPCs at 2h and 24 h after surgery (the clinical outcome definitions of PPCs will adopt European joint taskforce guidelines published in 2015 [38]. These include respiratory infection, respiratory failure, atelectasis, pleural effusion, pneumothorax, bronchospasm, aspiration pneumonia, pulmonary edema, ARDS, tracheobronchitis, pulmonary edema, exacerbation of pre-existing lung disease, pulmonary embolism).

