### Sample size calculation and statistical analysis

According to previous studies, the incidence of atelectasis is approximately 90% in patients pre-oxygenated with 100% oxygen within a few minutes after anesthesia [1, 4, 33, 39]. We estimate that the incidence of atelectasis is 85%, and the preoperative administration of S-ketamine can reduce the incidence of atelectasis to 60%. The sample size was calculated by PASS 15.0. Finally, 50 cases in each group will be estimated to provide 80% power with a significance level *α* of 0.05, allowing for a dropout rate of 5%.

Statistical analysis will be performed using SPSS 24.0. Values will be expressed as mean ± standard deviation ($$\overline{x }$$±s), median and interquartile range (IQR), and percentages according to different distribution types. After testing for normality of continuous variables, Student’s *t*-test or the Mann–Whitney *U*-test will be used for comparison between and within groups, as appropriate. Categorical variables will be analyzed using the chi-square test or Fisher’s exact test. All statistical analyses in our study will be conducted with a bilateral test, and statistical significance will be set at *P* < 0.05. We will exclude patients whose primary data are missing. Both intention-to-treat analysis and per-protocol analysis will be conducted in this study.

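### Dropout and termination rules can end a patient's follow-up before the 2 h and 24 h assessments, for events that are, or may overlap with, the complications counted there

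*Protocol article*

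**What the plan says.** Two sections of the protocol article deal with events after allocation.

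- *Dropout criteria* lists four items: a tube that has to stay in after surgery, repeat surgery within the same admission, perioperative "complications such as pneumothorax and subcutaneous emphysema which make lung ultrasound assessment" difficult, and withdrawal. The three clinical events stand in one list with withdrawal, with no distinction in consequence.
- *Criteria for discontinuing or modifying the allocated interventions* says that "the study will be terminated in the following situations: (1) intraoperative serious adverse events, such as hemorrhage, shock, and malignant hyperthermia", and adds as a second situation "without anticipated difficult airway or failure to extubation after surgery".

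*Secondary outcomes* includes "the incidence of postoperative complications associated with S-ketamine at 2 h and 24 h after surgery" and PPCs at the same two times. Of the PPC components it says: "These include respiratory infection, respiratory failure, atelectasis, pleural effusion, pneumothorax, bronchospasm", among others. PPCs belong to the stated objective in *Background*, which is to "further investigate the effects of preventing the early formation of perioperative atelectasis and PPCs" once the primary question is answered.

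On analysis, *Sample size calculation and statistical analysis* says: "We will exclude patients whose primary data are missing. Both intention-to-treat analysis and per-protocol analysis will be conducted in this study".

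**The concern.** The allocated treatment is one injection given 5 min before induction (*Interventions*). By the time any of the listed events occurs, no allocated treatment is left to stop or change. A rule that drops the patient or terminates the study can then act only on what is still to be observed: for most of these events, the T3 scan and the 2 h and 24 h assessments.

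Difficulty in scanning is a good reason to omit a scan. It is no reason to omit a bedside check for complications, which needs no study scan. One trigger is itself an outcome event and another may be, so the patients whose follow-up ends could be those most likely to count as PPC cases. An analysis plan can define analysis sets later, but it cannot recover an assessment that was never made.

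**Working it through.** **Step 1. Timing of each trigger against what remains.** All triggers follow randomisation, because the syringe is prepared from the allocation before surgery (*Allocation concealment mechanism*). T2 is 15 min after intubation; T3, the last scan, precedes extubation (*Interventions*).

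| Trigger | Section | When | Assessments at risk | Overlap with a PPC component |
|---|---|---|---|---|
| Pneumothorax or emphysema hindering ultrasound | Dropout | up to T3, since no scan follows | T3 scan, 2 h, 24 h | direct for pneumothorax |
| Retained tube / failed extubation | Dropout / Discontinuing | end of surgery | 2 h, 24 h | possible (respiratory failure) |
| Repeat surgery | Dropout | after T2; no time limit given | 2 h or 24 h if early; none if after 24 h | none stated |
| Intraoperative serious adverse event | Discontinuing | during surgery | T3 scan, 2 h, 24 h (T2 too if very early) | the named examples are not listed PPCs |
| Unforeseen difficult airway | Discontinuing | at intubation, before T2 | possibly all | none stated |

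Only pneumothorax is plainly both a reason to drop out and a counted outcome. Dropping a patient for repeat surgery after 24 h serves no purpose, because every planned assessment is then complete.

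**Step 2. The plan's own figure.** Inputs from *Sample size calculation and statistical analysis*: 85% against 60%, two-sided α 0.05, power 80%, dropout 5%. With unpooled variance,

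n = (1.960 + 0.842)² × (0.85×0.15 + 0.60×0.40) / 0.25² = 46.15, so 47 per group; 47 / 0.95 = 49.5, so 50.

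The stated 50 per group is reproduced. (The pooled formula gives 49, or 52 after inflation.) The planned loss is 5% of 100 = 5 patients.

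**Step 3. How much uncertainty a lost patient adds.** This needs no assumed PPC rate. With k₁ and k₀ patients of unknown PPC status in arms of 50, the width of the worst-case bounds on the risk difference is k₁/50 + k₀/50:

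- one patient lost: 1/50 = 2 points
- one per arm: 1/50 + 1/50 = 4 points
- the whole planned loss, split 2 and 3: 2/50 + 3/50 = 10 points

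The last figure is an upper bound, because the 5% also has to cover withdrawals.

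**Step 4. Scale against sampling error.** The article gives no PPC rate, so the incidences here are assumptions. The standard error of the difference is √(2p(1−p)/50):

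- p = 5%: 4.4 points
- p = 12%: 6.5 points
- p = 20%: 8.0 points

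One lost patient (2 points), or one per arm (4 points), therefore lies within one standard error.

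**Step 5. Scale against the number of events.** At an assumed overall incidence p, the trial expects 100p events. One lost PPC case is 1/5 = 20% of them at 5%, 1/10 = 10% at 10%, and 1/20 = 5% at 20%.

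**The case against.** The strongest reply is that nothing in the article says follow-up stops. *Dropout criteria* attaches no consequence for the 2 h and 24 h assessments, and reading the termination sentence as ending one patient's participation is an inference. *Allocation concealment mechanism* says that deviations and missing data are recorded, and a full protocol or analysis plan may settle how such patients are handled. This stands in part. The inference is nevertheless the natural one: the events share a list with withdrawal, no treatment remains to be stopped, and ending the whole trial over one haemorrhage would make less sense. The point rests on rules the article states, not on detail it omits.

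The second reply is that the patients are ASA I–II, aged 18–60, with BMI up to 30, normal chest imaging and no expected airway difficulty, so the events will be few. The pneumothorax rule applies only when scanning is hindered. In a patient who stays intubated, dizziness or nightmares may not be assessable at 2 h even if follow-up continues. All of this stands, and it keeps the point minor.

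Three stronger readings are tempting and are not supported:

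- *That recorded T2 scores are discarded, or that intention-to-treat is broken for the primary outcome.* The statistical section excludes only patients whose primary data are missing. A patient with a T2 score and a later event therefore stays in, and the per-protocol set is a natural place for the dropout criteria.
- *That the PPC comparison will be materially biased.* Such a scenario can be built: with equal true risks of 20%, removing half of the PPC cases in one arm and a quarter in the other gives 11.1% against 15.8%, a spurious 4.7 points. But that means 5 + 2.5 = 7.5 losses, all PPC cases, which is more than the 5 losses planned from every cause. The documents support no such fractions.
- *That the 5% allowance conflicts with the dropout rules.* It contradicts nothing.

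**Conclusion.** The point holds as a minor one. On their natural reading, the two sections end participation for events after randomisation, before the 2 h and 24 h assessments of PPCs and S-ketamine complications. Pneumothorax is directly both a dropout reason and a PPC; a retained tube or failed extubation may overlap with respiratory failure. The patients lost may therefore not be a random subset for these secondary and safety outcomes. Each one leaves the PPC risk difference open by 2 points, with a ceiling of 10 if the whole 5% allowance were used this way. The likely number is small, and the size and direction of any bias are unknown because the article gives neither a PPC rate nor a rate for the trigger events. The conclusion assumes that dropout and termination end the individual patient's follow-up, which the article implies but does not state. No material effect on the primary outcome is claimed.

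**What to change.** Four changes of wording:

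1. In *Criteria for discontinuing or modifying the allocated interventions*, replace termination of the study with: study procedures that can no longer be done in that patient (for example the T3 scan) will be stopped.
2. In *Dropout criteria*, use every item except withdrawal only to define the per-protocol set. Patients with a T2 score then stay in the intention-to-treat analysis, as the statistical section already implies.
3. State that the blinded 2 h and 24 h follow-up continues after any of these events unless consent is withdrawn.
4. State that a perioperative pneumothorax counts as a PPC, whether or not it prevented a scan.

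The cost is a short amendment and a few more follow-ups, at most about 5 at the planned loss, by the blinded assistants already in place. It needs no added recruitment, no unblinding and no change to the sample size.

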### Allocation, randomization, and blinding

The study investigator will be trained to implement standardized intervention methods.

#### Sequence generation

An independent statistician will perform randomization using a computer random number list generated by Stata software version 15.1. Participants will be randomly assigned to either the S-ketamine group (group 1) or the normal saline group (group 2), and the allocation ratio will be 1:1.

#### Allocation concealment mechanism

Group allocations will be sealed in sequentially numbered opaque envelopes. An independent study researcher who is not involved in anesthesia management or data collection will obtain randomized allocation information and prepare the study agents in the opaque 5-mL syringes before surgery. The blinded anesthesiologists in charge will use the study agents during anesthesia induction to complete the intervention and record the intraoperative data. Two well-trained anesthesiologists will perform lung ultrasound assessments and record LUS at relevant time points. Blinded and trained research assistants will perform the postoperative follow-up 24 h after the operation to record relevant data. All deviations or missing data will also be recorded.

#### Blinding

In this study, anesthesiologists in charge, patients, lung ultrasound assessors, and follow-up staff will be blinded to the randomized information. After all the results are completely analyzed, the blinding will be stopped.

### Criteria for discontinuing or modifying the allocated interventions

The assignment will not be modified; however, the study will be terminated in the following situations: (1) intraoperative serious adverse events, such as hemorrhage, shock, and malignant hyperthermia, and (2) without anticipated difficult airway or failure to extubation after surgery.

